### Randomization, allocation, and concealment

2.4

A research assistant at each clinical institution will conduct random assignments independently from other study activities. Eligible patients will be randomly assigned into the verum acupuncture plus placebo group, itopride plus sham acupuncture group, and sham acupuncture plus placebo group in a 1:1:1 ratio. A professional statistician will utilize SAS software (v9.3) to produce a list of random numbers stratified by clinical institution using block sizes of 6 or 9. The randomization process will be carried out through an online central randomization system. The randomization number and group assignment provided to each patient by the randomization system will be unique and unchangeable, ensuring fairness in treatment allocation.

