### Outcome

2.7

Primary outcomes in this study include the proportion of responders (PR) and the elimination rate of the main symptom. The secondary outcomes include changes in symptom score, QOL, mood during the treatment and follow-up, and the participants’ expectancy for acupuncture before treatment, as well as related hormone concentrations. Table 2 display a summary of all measurements. Follow-up for all participants can be completed via social media (WeChat) or phone.

**Table 2 tab2:** SPIRIT figure for the schedule of enrollment, interventions, and assessments.

	Study period								
	Enrolment	Allocation	Treatment phase				Follow-up		
Timepoint**	*1w*		*2w*	*3w*	*4w*	*5w*	*9w*	*13w*	*17w*
Enrolment									
Eligibility screen	X								
Informed consent	X								
Allocation		X							
Interventions									
Verum acupuncture plus placebo									
Itopride plus sham acupuncture									
Sham acupuncture plus placebo									
Assessments									
Proportion of responders			X	X	X	X	X	X	X
Elimination rate			X	X	X	X	X	X	X
NDSI		X				X	X	X	X
SF-NDLQI		X				X	X	X	X
HADS		X				X	X	X	X
Acupuncture expectation		X							
Related hormone concentrations		X				X			
Adverse events			X	X	X	X			

SPIRIT, standard protocol items: recommendations for interventional trials; NDSI, the nepean dyspepsia symptom index; SF-NDLQI, the short form - Nepean Dyspepsia Life Quality Index; HADS, Hospital Anxiety and Depression Scale.

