**Laboratory tests** Serum levels of motilin, gastrin, and ghrelin will be measured using enzyme-linked immunosorbent assays. Fasting venous blood samples (2 mL) will be collected at baseline and after 4 weeks of treatment from all study participants and stored at −80°C until analysis. Laboratory tests will be performed by trained laboratory professionals blinded to treatment assignment.

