### Statistical analysis

2.12

Efficacy analyses will be performed on all patients who were randomized, adhering to the intention-to-treat principle. This approach ensures that all patients are included in the analysis based on the group to which they were initially assigned, regardless of whether they completed the study as intended. Missing data on the primary outcome will be imputed using the multiple imputation method under the missing at-random assumption. If there are significant differences in baseline variables between the two groups, those unbalanced variables will be included as covariates in the analysis of the primary outcome.

We will establish confidence intervals at a 95% level, with a significance level set at 0.05. Continuous data will be reported as mean ± standard deviation (SD) if it is normally distributed. Otherwise, it will be reported as median (interquartile range). For longitudinal continuous data, we will compare groups using repeated-measures analysis of variance (ANOVA), taking into account both group and time-group interactions. Student’s t-test or Wilcoxon rank-sum test will be used for other continuous data. For categorical data, Χ^2^ test or Fisher’s exact test will be applied as appropriate. The strength of linear relationships between variables will be evaluated using linear correlation analysis, and sensitivity analysis will be performed if required. The occurrence of AEs between groups will be summarized using descriptive analysis.

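### The plan does not fix which continuous-data rule covers the three hormone outcomes, and neither rule adjusts for the baseline sample, so the comparison is less precise than a baseline-adjusted model

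*Protocol article*

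**What the plan says.** **Outcomes and timing.** Under laboratory tests in section 2.7.2, "Serum levels of motilin, gastrin, and ghrelin will be measured using enzyme-linked immunosorbent assays". Samples "will be collected at baseline and after 4 weeks of treatment from all study participants". Table 2 agrees: hormones are marked in the allocation column and at week 5 only. Section 2.7 speaks of change for symptom score, quality of life and mood, but adds the hormones simply "as well as related hormone concentrations".

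**Arms.** Section 2.4 randomises to verum acupuncture plus placebo, itopride plus sham acupuncture, "and sham acupuncture plus placebo group in a 1:1:1 ratio".

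**Analysis rules.** Section 2.12 gives two rules for comparing groups on continuous data. The first is "For longitudinal continuous data, we will compare groups using repeated-measures analysis of variance (ANOVA), taking into account both group and time-group interactions". The second, for everything else, is that Student's "t-test or Wilcoxon rank-sum test will be used for other continuous data". A mean with SD is reported for a variable "if it is normally distributed", and a median with interquartile range otherwise. Covariates are mentioned only for the primary outcome, and only for baseline variables that turn out to be unbalanced.

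**The concern.** An outcome with one baseline and one later value could be placed under either rule, and the section does not place it. Several analyses would therefore comply with the plan: a time-by-group test, a t-test or rank-sum test on week-5 values, or either test on change from baseline. They differ in precision, and the mean-based and rank-based versions do not estimate the same quantity. If the choice is made once the data are in hand, the three hormones could be reported on different scales.

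All of these options also give up precision. The baseline blood draw and assay are already planned for every participant, and the baseline value is usually the strongest predictor of the later one. No stated rule uses it as a covariate for a secondary outcome. Finally, the residual rule names only two-sample tests in a three-arm trial and does not say which pairs of arms are compared.

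**Working it through.** **The plan's own figure.** The document gives no SD, effect size or correlation for any hormone. Its only sample size is for the responder outcome (section 2.11), and it is used here only to fix the number per arm. With rates 0.7069 and 0.5546, margin 0.10, one-sided alpha 0.025 and power 80%:

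n = (1.960 + 0.842)² × (0.7069 × 0.2931 + 0.5546 × 0.4454) / (0.7069 − 0.5546 + 0.10)² = 7.849 × 0.4542 / 0.06366 = 56.01, rounded up to 57.

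This reproduces the stated 57 per group.

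**Inputs for the check.**
- 57 evaluable patients per arm (section 2.11, before the dropout allowance).
- The within-arm correlation r between baseline and week-5 values is an assumption, shown at 0.3, 0.5 and 0.7.
- The variance is assumed equal at both times and set to 1.

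**Formulas.** Variance per patient entering the comparison of two arms:
- week-5 value only: 1
- change from baseline: 2(1 − r)
- ANCOVA on baseline: 1 − r²

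ANCOVA relative to a week-5 test is therefore 1 − r². Relative to a change score it is (1 − r²) / [2(1 − r)] = (1 + r)/2.

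With two time points, the time-by-group test of a repeated-measures ANOVA is the change-score test. A numerical check with two arms of 57 gave an interaction F of 7.575 and a squared change-score t of 7.575.

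| r | Week-5 value | Change or time-by-group | ANCOVA | ANCOVA ÷ week-5 | ANCOVA ÷ change |
|---|---|---|---|---|---|
| 0.3 | 1 | 1.40 | 0.91 | 0.91 | 0.65 |
| 0.5 | 1 | 1.00 | 0.75 | 0.75 | 0.75 |
| 0.7 | 1 | 0.60 | 0.51 | 0.51 | 0.85 |

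The ratios in the last two columns are below 1 in every row, so the result does not depend on which rule is meant to apply. At r = 0.5, matching ANCOVA with 57 per arm would take 57/0.75 = 76 per arm with either unadjusted method.

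**Illustration in power.** For an assumed difference of 0.5 SD, two-sided 0.05 and 57 per arm, power is Φ(0.5/√(2v/57) − 1.96), where v is the variance in the table:

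| r | Week-5 t-test | Change or time-by-group | ANCOVA |
|---|---|---|---|
| 0.3 | 76.1% | 61.6% | 79.9% |
| 0.5 | 76.1% | 76.1% | 86.9% |
| 0.7 | 76.1% | 93.1% | 96.2% |

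The ratios hold for mean-based comparisons on whatever scale is analysed. They do not carry over exactly to the rank-sum test.

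**The case against.** The case against acting has four parts.

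**The baseline may well be used.** A reader might infer that the hormones belong to the residual rule and that their baseline is therefore discarded. The text does not support this. Two measurements in the same patient can be called longitudinal, and the time-by-group test uses the baseline. Even a t-test or rank-sum test could be run on change. The residual rule also has another natural target in the expectation score, which is measured only once. This objection stands: the plan specifies no baseline adjustment, which is less than saying that it ignores the baseline.

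**Normality is not stated as the test criterion.** A reader might also infer that a normality check decides between t-test and rank-sum test. Section 2.12 ties normality to the descriptive summary; for the tests it gives no criterion at all. A normality-based choice is the natural reading but not the stated one. What remains is that the choice is not fixed.

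**Skewness and magnitude come from outside.** Nothing in the document says that these hormones are skewed, and it gives no SD, effect or correlation. This stands, so the ratios are shown over a range and the log scale is offered only conditionally. At high r the gain over a change score is modest (93.1% against 96.2% power at r = 0.7).

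**Validity and level of detail.** In a randomised comparison, unadjusted tests and change scores are valid, and a journal article may leave the details of secondary analyses to a fuller plan. Both statements are true. The point therefore rests only on what section 2.12 does state: two rules whose boundary is unclear for these outcomes, both less precise than a simple alternative.

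**Conclusion.** The point holds as a matter of precision and prespecification, not of bias. The article does not make clear which of its two rules covers motilin, gastrin and ghrelin, and it states no baseline adjustment for secondary outcomes. Relative to ANCOVA, a week-5 test has 1/(1 − r²) times the variance: 1.10, 1.33 and 1.96 at r = 0.3, 0.5 and 0.7. A change-score or time-by-group test has 2/(1 + r) times: 1.54, 1.33 and 1.18. These figures rest on assumed correlations and on equal variance at the two times; the direction holds for any r between 0 and 1. If the residual rule applies, the choice between a mean-based and a rank-based test is open as well.

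The documents do not support saying that the baseline is certainly unused, that a normality check certainly selects the test, or that the planned tests are invalid. The matter is confined to three secondary laboratory outcomes and touches neither the primary analysis nor the sample size.

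**What to change.** In section 2.12, state one method for the three hormones: for each, an ANCOVA of the week-5 value on its own baseline value, arm (all three arms in one model) and institution, the stratification factor. Name the pairwise contrasts (verum against itopride, verum against sham, itopride against sham) and report each with a 95% interval. Say that neither the repeated-measures rule nor the residual t-test or rank-sum rule applies to these outcomes.

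Fix the scale before data are seen. If skewness is expected, log values at both times with ratios of geometric means are reasonable; otherwise use adjusted mean differences. That expectation is for the investigators to state, since the article gives no basis for it.

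The cost is one sentence and no extra samples or visits. Results would appear as adjusted differences or ratios rather than as raw group comparisons.

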### Dissemination policy

2.13

We intend to publish the final trial results in medical journals related to functional gastrointestinal disorder or complementary and alternative medicine (CAM) within 2 years of completing the final data collection.

## Discussion

3

There has been a growing focus in academia on effective treatment for FD in recent years. While some advancements have been achieved in drug treatment for FD (8), the effectiveness is not satisfactory and may come with side effects (9, 10). These problems compel patients to explore other safer and more effective methods in CAM. Acupuncture, a non-pharmacologic therapy in TCM, has been observed to be effective in reliving upper abdominal discomfort and improving QOL in FD patients (13, 14). However, there remains a lack of high-quality clinical studies and evidence supporting the use of acupuncture for FD treatment (8). This study aims to assess the efficacy and safety of acupuncture for FD in a well-controlled trial design, providing evidence to support the clinical application of acupuncture.

For better clinical management, the Rome III Consensus proposed a symptom subtype classification of FD, and Rome IV Consensus adhered to this method (31). Although it remains controversial whether there is any difference in pathogenesis between PDS and EPS (32), choosing a treatment plan based on FD subtypes has become a new trend (33). Evidence shows that PDS is the most prominent subtype, affecting more than 60% of all FD patients (3, 4). Therefore, we selected PDS patients as the subjects of this study and diagnosed FD-PDS patients based on Rome IV criteria. Though multiple mechanisms contribute to PDS development, gastric sensorimotor function disorder has been considered a vital factors (33). Prokinetic agents have been recommended as the first-choice treatment for PDS patients in a Chinese consensus (34). Itopride is a prokinetic agent with a response rate of 55–73% in treating FD and higher drug safety (30, 35, 36). Therefore, we used itopride as a positive drug to evaluate the efficacy of acupuncture in treating PDS, thereby providing more clinical treatment decision-making references.

Five acupoints are selected in this protocol based on findings from clinical and basic research: Sibai (ST2), Zusanli (ST36), Liangmen (ST21), Neiguan (PC6), and Gongsun (SP4). A previous clinical study has shown that acupuncture at above five acupoints can further alleviate discomfort in upper abdominal and improve patients’ QOL based on mosapride treatment (22). ST2, ST36, and ST21 belong to the Yangming stomach meridian of the foot, commonly applied in digestive-system diseases. These three acupoints can regulate the disturbed qi and blood and normalize spleen and stomach function. In particular, acupuncture at ST36 has been proven to improve the gastric function of FD model rats by reducing low-grade inflammation of duodenal mucosal, accelerating gastric emptying, and reducing gut visceral hypersensitivity (37, 38). PC6 and SP4 are both Ba-mai Jiao-hui points. The traditional meridian theory believes that stimulating PC6 and SP4 can positively affect the gastrointestinal tract function and emotional state. Our previous basic studies indicated that acupuncture at PC6 and SP4 could improve gastrointestinal motility disorders, visceral hypersensitivity, and the anxiety and depression-like behavior in rats with FD (39, 40). Therefore, we selected ST2, ST36, ST21, PC6, and SP4 as our acupuncture acupoints.

To our knowledge, this is the first multicenter, randomized, double-dummy, single-blind, active-controlled trial assessing the efficacy and safety of acupuncture for treating PDS. In this trial, we will implement blinding among participants to reduce the potential influence of patient preference for acupuncture on the study results. Furthermore, we plan to adopt stringent quality control measures, blinded outcome assessments, ensured concealed treatment allocation, and intention-to-treat analysis to minimize bias and enhance the credibility of our findings. However, several limitations of this trial should be noted. Although participants and assessors are blinded in this trial, treatment personnel can not be further blinded due to the inherent nature of acupuncture. Therefore, it cannot be ruled out that performance bias influences the results. Second, this trial only includes patients from Changsha City; whether the results can be applied to other populations or regions requires further research. Finally, the proposed acupuncture regimen is standardized dose not account for individual differences among patients, which may limit the efficacy of the acupuncture treatment.

To summarize, the outcome of this study aims to validate the difference of effectiveness and safety between acupuncture and Itopride in treating PDS. These results will serve as a dependable foundation to endorse the practical use of acupuncture in managing FD.

## Trial status

This clinical trial is in progress. Recruitment is scheduled to begin in December 2024 and be completed by December 2027.
